### Participants

Patients will be screened in the emergency department of a large University-affiliated hospital and will be enrolled in the fracture clinic. Table 1 lists eligibility criteria for the study. Enrolled patients include males and females > age 60 with acute (< 3 weeks) displaced proximal humerus fractures that fall into the Neer category of 3- or 4- part. Diagnosis will be obtained from radiographs including a true AP (neutral rotation) of the shoulder, a lateral Y-view and an axillary (or trauma axillary) view. The fractures reviewed for inclusion will be independently assessed by two Orthopaedic Surgeons participating in the trial. If there is any disagreement on the classification or inclusion, a third surgeon will be asked to review. The majority consensus will be the implemented inclusion and classification. Eligible patients that have consented to participate in the study will receive informed consent on the two treatment arms prior to randomization. Preoperative baseline functional assessment including the Constant, ASES, EQ-5D-5 L, PROMIS and IPAQ scores will be completed. Patients randomized to the surgical arm will undergo surgery within 7 days of presentation.

**Table 1 Tab1:** Inclusion and Exclusion Criteria

Inclusion Criteria	
1. Displaced 3-part proximal humerus fractures by the Neer classification; or displaced 4-part proximal humeral fractures by the Neer classification that are deemed amenable to surgical internal fixation	
2. > 60 years of age	
3. Low energy mechanism of injury	
4. Acute fracture^a^	
Exclusion Criteria	
1. 4-part proximal humerus fractures that are not deemed amenable to surgical fixation^b^; fractures that are better suited to treatment with arthroplasty	
2. Isolated greater tuberosity fractures	
3. Ipsilateral upper extremity significant injury, concomitant fracture or polytrauma	
4. Open fracture	
5. Previous ipsilateral shoulder surgery	
6. Patients with active worker’s compensation claims^c^	
7. Active joint or systemic infection	
8. Patients with convulsive disorders, collagen diseases, and any other conditions that might affect the mobility of the shoulder joint	
9. Major medical illness^d^	
10. Unable to speak or read English/French	
11. Psychiatric illness that precludes informed consent	
12. Unwilling to be followed for 2 years	

^a^ <3 weeks

^b^due to osteopenic bone, thin head or tuberosity fragments

^c^due to the expectation of lower rates of success in this patient population

^d^life expectancy less than 2 years, unacceptably high operative risk, or not medically cleared by preoperative anesthesia consult

### Sample size calculation

The sample size will be 160 patients. The minimum clinically important difference for the Constant score is 12 [52, 53], with standard deviation of 23.1 from measurements in previous studies of similar patient populations. For the primary outcome, to achieve 80% power to detect a clinically meaningful difference of 12 points on the Constant score, with standard deviation of 23.1, and alpha of 0.05, a sample size of approximately 116 people would be necessary (58 per arm). The overall sample size is increased from 116 to 129 to account for an expected 5% crossover from the non-operative study arm to the operative study arm. An additional 31 patients were added for a conservative sample size adjustment accounting for 20% loss-to-follow-up over the two years of follow-up, for a total sample size of 160 patients.

### Randomization and blinding

Figure 1 shows the flow of procedures in the trial. Study group allocations will have been pre-determined from an online randomization generator and catalogued in sealed envelopes by personnel independent of the study. The allocation will be in a 1:1 ratio, stratified by fracture type (3 and 4 part): 3- and 4-part fractures will be stratified using permuted blocks of variable length (4 to 6). Randomization and allocation to treatment will be determined on the day of the first assessment in the plaster room clinic within 7 days post injury or at the time of the emergency room visit if the patient is unable to return home. The research coordinator will open the sealed envelope containing the study allocation and will inform the surgeon of the patient’s assigned treatment: non-operative or ORIF treatment. Patients assigned to the ORIF group will have surgery scheduled within 7 days following injury.

**Fig. 1 Fig1:**
[figure not shown]
Flow of patients through the trial

The research coordinator will enter all necessary patient information into a password protected electronic database, however due to the nature of the trial design, it is not possible for the surgeon (or the patient) to remain blinded to treatment allocation. The research coordinator will carry out the follow-up assessments and will remain blinded to the patient’s treatment allocation and will not have access to the participant’s chart or radiographs prior to or during the assessment. This will minimize the potential for biases introduced by the examiner when performing the physical assessment and recording data. To help reduce the potential for observer bias, the physical examination and the administration of study questionnaires are standardized. A trained musculoskeletal radiologist [name] will perform the radiological assessments.

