**Methods:**

We will conduct a prospective, single blind randomized controlled parallel arm trial to compare non-operative management of proximal humerus fractures with open reduction and internal fixation using locked plating technology. One-hundred and sixty patients > age 60 with acute 3- or 4- part proximal humerus fractures will be randomized to either open reduction and internal fixation with locked plating technology or non-operative management treatment arms. The primary outcome measure is the Constant Score at 24 months post-operative. Secondary outcome measures include the American Shoulder and Elbow Surgeon’s Score (ASES), EuroQol EQ-5D-5 L Health Questionnaire Score, short form PROMIS upper extremity score and IPAQ for the elderly score. Further outcome measures include assessment of the initial classification, displacement and angulation and the quality of surgical reduction via a standard computed tomography (CT) scan; rates of non-union, malunion, arthrosis, osteopenia or other complications including infection, nerve injury, intra-articular screw penetration, reoperation rates and hospital re-admission rates.

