## Methods

### Study design

This study is designed as a single-centered prospective, single blind, randomized controlled trial (RCT) with parallel arms comparing nonoperative management with locked plate open reduction and internal fixation (ORIF) of proximal humerus fractures. After enrollment, patients will be randomly allocated to receive either nonoperative or operative fixation of their proximal humerus fractures. This study will abide by the current international research standards and will be reported as per the guidelines in the CONSORT statement [51]. Approval was obtained from the Health Science Network Research Ethics Board of Ottawa and is in compliance with: Ethical Conduct for Research Involving Humans; the International Conference Harmonization Good Clinical Practice: Consolidated Guideline and the provisions of the Personal Health Information Protection Act 2004. All surgical procedures will be performed by fellowship trained shoulder surgeons in a large University-affiliated hospital.

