## Discussion

The optimal management of proximal humeral fractures remains controversial [4]. Three previous randomized studies have not demonstrated a difference in patient-centered outcomes between non-operative treatment and open reduction internal fixation [44, 45]. Two of these studies, however, had relatively small numbers of patients. Surgical complications and mortality may occur with increased frequency in the elderly [42] and as such, avoidance of unnecessary surgery would decrease patient morbidity and decrease cost to the health care system.

The PROFHER trial [39] is currently the largest multi-centered randomized controlled trial to compare operative vs nonoperative treatment of proximal humerus fractures. The trial did not show a significant difference in functional outcome between treatment groups using the Oxford and SF-12 functional outcome scoring. The PROFHER trial had a few methodological limitations that the authors of the current study have sought to address. The PROFHER trial included patients from age > 16 years. The functional demands in younger patients differ and are not necessarily generalizable to older patients. Although there was a subgroup analysis for age < 65 and > 65, having wide age inclusion criteria makes interpretation of the results difficult. The current trial inclusion criteria limits the study to patients over the age > 60. Other limitations in the PROPHER study included lack of blinding, the inclusion of hemiarthroplasty in the surgical arm, lack of standardization between rehabilitation programs in the operative and nonoperative arms, and very low enrollment in certain centers; all of these potential shortcomings have been addressed in the current trial including blinding of research personnel, limiting surgical treatment to ORIF, standardization of rehabilitation protocols, and limiting enrollment to a large, high-volume, tertiary care center.

Further potential strengths include the use of pre-operative CT scan for analysis of fracture displacement/angulation, and inclusion of the IPAQ score, which is tailored towards the elderly population in order to assess the functional demands of the population within the study and how this impacts performance on the other functional assessment tools.

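### The research coordinator both opens the allocation envelope and is the assessor who must stay blinded, so the single-blind claim is not supported as written

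*Protocol article*

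**What the plan says.** The Study design section describes the trial this way: "This study is designed as a single-centered prospective, single blind, randomized controlled trial (RCT) with parallel arms". The Methods paragraph of the Abstract uses the same blinding label.

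The section Randomization and blinding gives the research coordinator three tasks:

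- At randomization: "The research coordinator will open the sealed envelope containing the study allocation and will inform the surgeon".
- For data handling, in the text after Fig. 1: "The research coordinator will enter all necessary patient information into a password protected electronic database".
- At follow-up, in the same paragraph: "The research coordinator will carry out the follow-up assessments and will remain blinded".

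Two safeguards are stated. The coordinator "will not have access to the participant’s chart or radiographs prior to or during the assessment", and the physical examination and questionnaires are standardised. On the other parties, the paragraph says that "it is not possible for the surgeon (or the patient) to remain blinded to treatment allocation". A radiologist reads the images and is not said to be blinded.

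The Abstract fixes the endpoint: "The primary outcome measure is the Constant Score at 24 months post-operative". The Constant score section says that the instrument emphasises range of motion and strength, with strength tested on a spring-loaded device.

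The Discussion lists lack of blinding among the limitations of the earlier large multicentre trial and then states: "all of these potential shortcomings have been addressed in the current trial including blinding of research personnel".

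**The concern.** One role is told the allocation and is later required not to know it. Both statements are explicit and stand in the same section, so this is a conflict between two stated rules and not a detail left out of a condensed article.

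The assessor carries the whole weight of the blinding. Patients and surgeons know the treatment by design, so if the assessor knows it too, no party is left to justify the label.

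The primary outcome makes this important. An examiner measures motion and strength for the Constant score, so expectations about treatment can enter the measurement. The article recognises this risk, since it gives blinding as the means of limiting examiner bias. The investigators also state in advance that they expect no difference in function, so bias could either create a difference or hide one. The claimed improvement over the earlier trial depends on the same safeguard.

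**Working it through.** **Step 1: the statements side by side (Randomization and blinding).**

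| Time | Task | Role named | Knowledge of allocation |
|---|---|---|---|
| Day of randomization | Opens envelope, tells surgeon the arm | Research coordinator | Necessarily known |
| 3, 6, 12 and 24 months | Follow-up assessment | Research coordinator | Said to remain unknown |

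The same title, with the definite article, is used both times. No second coordinator or independent assessor is named. The section Compliance and loss of follow-up mentions a research assistant who telephones patients, but gives that role no part in allocation or assessment.

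**Step 2: do the stated safeguards resolve it?** Keeping the chart and radiographs away closes two later sources of information. It does not remove what was read in the envelope. Standardising the examination narrows the room for examiner influence but does not make the examiner blind. The article does not claim that the allocation is forgotten, and the first follow-up assessment comes only 3 months after injury.

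**Step 3: is anyone else blinded?** Surgeon: no, stated. Patient: no, stated. Radiologist: not stated. The single-blind label and the Discussion's claim therefore rest on the coordinator alone.

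**Step 4: the plan's own figure, for context.** The point disputes no number. From Sample size calculation: difference 12, SD 23.1, power 80%, two-sided alpha 0.05.

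n per arm = 2 × (1.96 + 0.8416)² × (23.1/12)² = 2 × 7.849 × 3.706 ≈ 58.2

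This rounds up to 59 per arm, or 118 in total, against the plan's approximate 116 (58 per arm). Power at 58 per arm is 0.799. The plan's figure is reproduced.

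**Step 5: illustration of what a bias would do.** Evaluable patients: 160 × (1 − 0.20) = 128, or 64 per arm.

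SE of the difference = 23.1 × √(2/64) = 4.08 points

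With no true effect and a constant examiner shift of b points in favour of one arm, the two-sided error rate is

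1 − Φ(1.96 − b/SE) + Φ(−1.96 − b/SE)

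| Assumed shift b | b/SE | Error rate, 64 per arm |
|---|---|---|
| 0 | 0 | 5.0% |
| 2 | 0.49 | 7.8% |
| 3 | 0.73 | 11.4% |
| 4 | 0.98 | 16.5% |

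With 58 per arm (SE = 23.1 × √(2/58) = 4.29), shifts of 2 and 4 points give about 7.5% and 15.4%. The values of b are assumptions; nothing in the documents supports any particular one.

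**The case against.** The strongest reply is that the article names a role and not a person. Two coordinators may share the title, one opening envelopes and the other assessing. The article condenses a fuller protocol, and the flow diagram is not available here. This is a fair limit on the conclusion: a reader might infer that the same individual will in fact do both tasks, or that the trial was run unblinded, and the documents do not establish either. What they do establish is that the procedure as written contradicts itself.

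Two further inferences are tempting but unsupported.

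- **The surgical scar.** A reader might infer that the incision will be visible to the examiner. The article says nothing either way about clothing or covering at the examination, and such detail is commonly left to the full protocol.
- **The database.** A reader might infer that data entry shows the coordinator the treatment arm. The text refers only to necessary patient information and does not say which fields that role sees. This is a reason to state the restriction when the text is corrected, not evidence of a second breach.

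It is also fair to say that a standardised examination and an instrumented strength test limit how far an examiner can move the score. That stands as mitigation but does not replace blinding.

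**Conclusion.** The contradiction is real and needs correcting. Followed as written, the plan gives no stated party blinding to allocation, so it does not deliver the single-blind design named in the Abstract and Study design or the advantage claimed in the Discussion. This affects the primary outcome because that outcome is partly examiner-measured.

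The conclusion rests on the text alone and on reading one role title consistently within one section. It does not rest on the error rates. A reader might take the range of about 8% to 16.5% as the trial's actual false-positive rate. It is not: it assumes a constant shift of 2 to 4 points favouring one arm, and the documents give no bias size and no evidence that one will occur. The sample size is unaffected.

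**What to change.** In Randomization and blinding, state that:

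1. opening the envelope, informing the surgeon and entering any data that reveal the allocation are done by an existing team member who never performs follow-up assessments; and
2. the follow-up assessor has no access to those data, in addition to the existing bar on chart and radiographs.

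Use different role titles for the two functions so that the text cannot be read as one person. If different people already fill them, one clarifying sentence is enough.

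If the roles cannot be split, remove the single-blind description from the Abstract and Study design, withdraw the statement that the assessor remains blinded, and drop the Discussion's claim to have addressed the earlier trial's lack of blinding.

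The cost is some clinic logistics, because randomization takes place in the plaster room clinic or at the emergency visit and the separate person must be available there. The article gives no staffing numbers, so the sponsor must confirm who can take the task. No additional patients are needed and the analysis does not change.

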#### Operative treatment

This trial will implement a standardized operative management protocol, using the Synthes TM (Synthes Canada, Mississauga, Ont., Canada) 3.5 mm LCP proximal humerus locking plate for open reduction internal fixation. Six fellowship-trained shoulder surgeons will perform the surgical fixation. Pre-operative medical clearance will be established via anesthesia consults if required for medically complex patients. Pre-operative intravenous (IV) antibiotic prophylaxis and administration of a general anesthetic will be utilized. Beach-chair position and the standard deltopectoral approach or minimally invasive plating technique will be utilized. The reduction technique will depend on the fracture pattern but key steps include disimpaction of the humeral head with anatomic reduction of the medial calcar and tuberosities. The locking plate will be positioned posterior to the bicipital groove at a target height of 5–8 mm distal to the tip of the greater tuberosity. Additional tuberosity suture fixation to the plate will be used when warranted. Provisional fixation, plate positioning and final fixation will be assessed with intraoperative fluoroscopy to ensure adequate reduction and hardware position. The surgical incision will be examined and staples removed 10–14 days postoperatively. The postoperative rehabilitation protocol will be identical to the nonoperative protocol as per above.

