### Outcome measures

Outcome measures are separated into primary and secondary as outlines below. All functional assessment scores will be completed at baseline and 3, 6, 12 and 24 months post injury. Complications and adverse events will be recorded on standardized case-report forms that will be completed immediately following the completion of the surgical procedure for patients randomized to the surgical treatment arm. At follow-up visits, clinical evaluation will be conducted to monitor for complications including infection, nerve injury, and hematoma formation or hospital re-admission.

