#### The American shoulder and elbow Surgeon’s (ASES) score [47]

The ASES score is a shoulder specific assessment tool developed by the American Shoulder and Elbow Society that consists of both patient self-assessment and physician assessment. It is a patient scoring system calculated from a self-assessment portion that evaluates pain and ability to perform tasks of daily living, and a clinical assessment which tests active range of shoulder motion and strength. The patient self-evaluation is divided into pain (recorded on a visual analogue scale) and activities of daily living (ADL, recorded on a numeric scale). The overall score is an equal weight of the two self-evaluation sections and produces a score out of 100 where 100 is the better outcome. The physician assessment is divided into four segments: range of motion, physical signs, strength and instability and does not provide a score.

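### The assessor's blinding is not secured as described: nothing stated conceals the surgical scar or stops patients disclosing their treatment before the Constant score is taken

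*Protocol article*

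**What the plan says.** In the protocol article, under Randomization and blinding (the text after Figure 1), neither surgeon nor patient can be blinded. The trial's single blind therefore rests on the assessor: "The research coordinator will carry out the follow-up assessments and will remain blinded to the patient’s treatment allocation". The concealment measure given is that this person "will not have access to the participant’s chart or radiographs prior to or during the assessment". The second safeguard is that "the physical examination and the administration of study questionnaires are standardized". From these the article concludes: "This will minimize the potential for biases introduced by the examiner when performing the physical assessment and recording data". The Discussion then counts blinding of research staff among the improvements over the earlier, larger multicentre trial.

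Other sections bear on whether the blind can hold:

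- **Operative treatment.** "Beach-chair position and the standard deltopectoral approach or minimally invasive plating technique will be utilized". The incision is closed with staples. The non-operative arm has no incision.
- **Constant score.** The primary instrument emphasizes range of motion and strength; strength is measured with a spring-loaded device.
- **ASES score.** "The physician assessment is divided into four segments: range of motion, physical signs, strength and instability". This physician part yields no score.
- **Outcome measures.** Functional scores are taken at baseline and at 3, 6, 12 and 24 months. "At follow-up visits, clinical evaluation will be conducted to monitor for complications including infection, nerve injury, and hematoma formation or hospital re-admission". The examiner is not named.
- **Randomization and blinding, on allocation.** "The research coordinator will open the sealed envelope containing the study allocation and will inform the surgeon of the patient’s assigned treatment".

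**The concern.** When surgeon and patient both know the treatment, the assessor's blind is the main protection for an outcome that an examiner partly determines. Keeping the chart and radiographs away closes one route by which the assessor could learn the arm. Two routes stay open in the text. One is the scar, at the body site being examined. The other is the patient, who knows the treatment and answers questions at the same visit. Using the same procedure for everyone reduces variation between examinations, but it does not keep the examiner from knowing who was operated on.

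If the arm becomes known, the examiner's expectation can enter the range-of-motion measurements and the encouragement given in strength testing. Purpose and hypothesis states that the investigators expect no difference in function, so the direction to worry about first is the masking of a real difference. A shift that favours one arm is also possible and would produce false positives. Neither is cured by enrolling more patients, because a bias does not shrink with sample size.

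**Working it through.** **1. Does the scar reveal the arm?** Sample size calculation expects 5% crossover from non-operative to operative treatment. With 1:1 allocation, and assuming that every patient assigned to surgery has it, a scar indicates assignment to ORIF with probability 1/(1 + 0.05) = 0.95, and absence of a scar indicates the non-operative arm. An assessor who sees the shoulder, or is told, knows the arm almost for certain.

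**2. Do the stated safeguards act on that route?**

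| Route | Stated measure | Closed? |
|---|---|---|
| Chart, radiographs | Withheld before and during assessment | Yes |
| Scar | None | No |
| Patient disclosure | None | No |
| Complication review at the same visit | Examiner and order not stated | Not determined |
| Allocation envelope | Opened by the role that also assesses | Contradictory |

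**3. The plan's own sample size.** Inputs from Sample size calculation: difference 12, SD 23.1, alpha 0.05 (taken as two-sided), power 80%.

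- Per arm: 2 × (23.1 × (1.960 + 0.842)/12)² = 58.2; the plan states 58 (116 in all). Power at 58 per arm is 79.9%.
- Crossover: 116/0.95² = 128.5; the plan states 129.
- Loss to follow-up: 129/0.8 = 161.25; the plan states 160.

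The figures reproduce within rounding. The sample size is not in question here.

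**4. What a given bias would do.** Evaluable per arm: 160 × 0.8/2 = 64. SE of the difference: 23.1 × √(2/64) = 4.08. The document gives no bias, so shifts b of 2 and 4 points are assumptions.

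- Power when the shift runs against a true 12-point difference: Φ((12 − b)/4.08 − 1.96).
- False-positive rate when the shift favours one arm and the true difference is zero: 1 − Φ(1.96 − b/4.08) + Φ(−1.96 − b/4.08).

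| Shift b | Power, 64 per arm | False positives, 64 per arm | Power, 58 per arm | False positives, 58 per arm |
|---|---|---|---|---|
| 0 | 83.6% | 5.0% | 79.9% | 5.0% |
| 2 | 68.8% | 7.8% | 64.5% | 7.5% |
| 4 | 50.0% | 16.5% | 46.2% | 15.4% |

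The 58-per-arm columns use SE = 23.1 × √(2/58) = 4.29 and show that the picture does not depend on which count is taken. The two effects belong to different scenarios: a pull toward equality costs power and does not create false positives.

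**The case against.** The strongest reply is that this is a condensed article. Garments, instructions to patients and the order of tasks within a visit usually sit in the full protocol or an assessor manual. That would settle the matter if the article were simply silent. It is not: it names its safeguards, says that they will minimize examiner bias, and advertises the result in the Discussion. The measures named do not support that claim.

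A reader might go further and infer that the shoulder is examined bare, that the coordinator asks about surgical complications during the scoring, and hence that the primary outcome is scored with knowledge of the arm. The document does not support this. It never says that the shoulder is uncovered. Complications are recorded at follow-up visits, but no examiner is named. The ASES signs are called a physician assessment, so they may already fall to someone else. What the text shows is an open route, not that unblinding occurs.

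Two mitigating points stand in part. Strength is read from a device, which limits the room for judgement, although effort and encouragement can still vary. The shift sizes have no anchor in the document, so the table is an illustration and not an estimate.

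It can also be said that the sharper problem is the envelope: the role that opens it is the role said to remain blinded. That contradiction is real and must be reconciled, but giving the envelope to another person would leave the scar and disclosure routes untouched.

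**Conclusion.** The concern holds in a limited form. Blinding of the assessor, claimed under Randomization and blinding and again in the Discussion, is not secured by the measures described. Whether it fails in practice, and by how much, cannot be read from the document. If knowing the arm moved scores 2 to 4 points toward equality, power for the 12-point difference would fall from about 84% to between 69% and 50%; if it moved them that far in favour of one arm, the false-positive rate would be about 8% to 17%. These figures assume SD 23.1, 64 evaluable patients per arm, a two-sided 5% test, a normal approximation and a shift shared by all patients in an arm. The change is worth making because the exposed outcome is the primary one and the remedy is cheap.

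**What to change.** Write the following into the blinding section:

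- At every follow-up visit, patients in both arms put on an opaque garment covering both shoulders before the assessor enters.
- Patients are told not to disclose their treatment to the assessor. The reminder call already planned before each appointment can repeat this.
- The assessor scores the Constant before any wound or complication review. Existing staff other than the assessor carry out that review and the physician part of the ASES.
- State that the assessor is not the person who opens the allocation envelope, so that the two statements about the research coordinator agree.
- Optionally, have the assessor record a guess of the arm, reported descriptively only. A correct guess may reflect the perceived outcome as well as a failed blind, so it should not decide whether the trial is called blinded.

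The cost is a garment, a sentence of instruction and a change in the order of the visit. The article does not say who attends each visit, so the availability of a second person should be confirmed. Patients are slightly inconvenienced, and landmarks for range of motion are marginally harder to see. The sample size does not change.
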